## Abstract

**Background:**

Tooth extraction procedures often lead to bone resorption, which can have adverse effects on the dimensions of the alveolar ridge. Research has shown that socket preservation techniques using bone graft substitutes can effectively minimize early bone loss in such cases. α–calcium sulfate hemihydrate (α-CSH) has garnered significant attention as a potential bone graft material due to its favorable properties, including osteoconductivity, angiogenic potential, and biocompatibility. Considering these facts, we developed a preliminary protocol for applying α-CSH in addressing alveolar bone loss following tooth extraction.

**Objective:**

This research’s general objective is to evaluate the feasibility and initial effectiveness of α-CSH as bone-inducing graft material for socket preservation after tooth extraction.

**Methods:**

This preliminary clinical trial will involve 30 fresh extraction sockets from individuals aged 18-35 years. The participants will be divided into 2 groups: one group will receive α-CSH graft material after tooth extraction for socket preservation, while the other group will not receive any graft material. Throughout the study, the participants will be closely monitored for safety measures, which will include clinical examinations, radiographic imaging, and blood tests. Radiographic imaging will be used extensively to assist the progress of bone formation.

**Results:**

The study commenced enrollment in August 2022 and is scheduled to conclude post assessments and analyses by the end of 2023. The results of the study are anticipated to be accessible in late 2024.

**Conclusions:**

This clinical study represents the initial investigation in humans to assess the feasibility and efficacy of α-CSH in alveolar bone regeneration. We hypothesize that the inclusion of α-CSH can greatly expedite the process of bone formation within fresh sockets, resulting in a swift restoration of bone height without the disadvantages associated with harvesting autogenous bone graft.

**Trial Registration:**

Indonesia Registry Center INA-D02FAHP; https://tinyurl.com/2jnf6n3s

**International Registered Report Identifier (IRRID):**

DERR1-10.2196/49922

## Introduction

Bone resorption is an ongoing and irreversible process that leads to changes in both hard and soft tissue dimensions, particularly occurring immediately after tooth extraction [1,2]. Various factors, such as chronic periodontitis, alveolar cleft, prolonged edentulous state, and tooth morphology, can contribute to alveolar bone resorption [3,4]. In addition, anatomical, prosthetic, functional, and metabolic factors have been identified as influencing factors in alveolar ridge resorption [5,6]. A previous study reported an average of 50% vertical resorption and 20% horizontal bone resorption occurring 8 weeks after tooth extraction [7]. Considering these findings, the dimensional changes in the alveolar bone following tooth loss raise significant concerns in oral rehabilitation [6,7].

In recent years, there has been a growing emphasis on developing techniques to preserve alveolar bone volume following tooth extraction [2,6,8]. Socket preservation procedures are recommended when tooth extraction significantly impacts the height of the buccal bone [9,10]. These techniques aim to minimize the biological resorption of the buccal bone, which facilitates implant placement and reduces the need for future bone augmentation procedures. Studies have shown that socket preservation techniques lead to greater bone volume compared to procedures without socket preservation [8,11]. In the future, sites that undergo grafting after tooth extraction are likely to require fewer bone augmentation treatments, particularly if implantation is planned [1,10]. Various biomaterials have been used to graft fresh extraction sockets, and most have demonstrated positive clinical outcomes [8,12,13].

α–calcium sulfate hemihydrate (α-CSH) has gained significant recognition as a bone graft substitute material with outstanding biocompatibility [14,15]. It has successfully repaired various bone defects, including resorbed maxilla, postextraction socket preservation, and significant segmental bone defects [14-16]. The α-CSH is regarded as a leading bone replacement material due to its ability to promote bone ingrowth and its resemblance to autologous bone [14,15,17]. Notably, it exhibits excellent workability, high self-setting strength, impressive osteoconduction properties, and the capacity to induce hemostasis and angiogenesis [14,17,18]. Despite these remarkable biological characteristics, this material still has to function better in clinical settings [15]. This study aims to evaluate the feasibility and preliminary efficacy of α-CSH as a bone-inducing graft material in socket preservation procedures following tooth extraction. Our hypothesis suggests that α-CSH will serve as a safe, efficient, and effective alternative to conventional autografts, as its regenerative properties complement its osteoconductive nature.

## Methods

### Ethical Considerations

The clinical trial was approved by the Ethics and Research Committee of Faculty of Medicine, Hasanuddin University, Makassar, Indonesia, with code number 504/UN4.6.4.5.31/PP36/2022. The study was designed according to the principles of the Declaration of Helsinki and will conform to the CONSORT (Consolidated Standards on Reporting Trials) statement [19].

Before participating in the study, all individuals must provide written informed consent, signifying their voluntary agreement to participate. Participants will have the opportunity to seek clarification on any aspects of the study and review all procedures, data collection methods, and data analysis protocols before signing the consent form. The informed consent document will comprehensively outline the research’s purpose, procedures, potential risks and benefits, as well as the confidentiality and security measures pertaining to the collected data. Participants will be explicitly informed of their entitlement to withdraw from the study at any point without experiencing any adverse consequences on their treatment.

Strict privacy and security protocols were implemented, and all study data were stored in a password-protected secure database. Each participant will receive a unique study code, and data sharing with operators and research assessors will be done in an encrypted format that maintains patient privacy. Participants will not be provided with any form of remuneration for their involvement in the study. Nonetheless, they will receive complimentary examination and treatment related to the trial without incurring any costs.

### Recruitment

Figure 1 presents a simplified diagram that outlines the study protocol based on the CONSORT diagram. The recruitment of participants and the implementation of the trial will take place at Hasanuddin Dental Hospital, Makassar, Indonesia. This hospital is the primary institution in the designated region that handles the majority of oral surgery cases. To identify eligible participants, all individuals presenting to the Department of Oral and Maxillofacial Surgery with a chief complaint related to the mandibular third molar will undergo screening conducted by the study investigators.

Before enrollment, all participants will be provided with detailed information regarding the risks and potential complications associated with the procedure, such as bleeding, infection, cheek asymmetry, parotid duct injury, potential injury to facial nerve branches, and the unlikely event of nonclosure. Informed consent will be obtained from each participant after ensuring their understanding and agreement.

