### Study Design

This prospective control clinical trial will be conducted at a single center and will involve 30 targeted extraction sockets after the removal of impacted mandibular third molars. This case is chosen as it represents a common scenario requiring extraction and often involving the removal of a significant amount of bone, making it an ideal model for studying human alveolar bone loss for socket preservation. The study aims to evaluate the efficacy of a high-purity α-CSH bioceramic (CaSO_4_·0.5H_2_O), synthesized from calcium sulfate dihydrate (CSD) without the use of chemical reagents, as a bone graft material in the alveolar bone loss case.

The 30 extraction sockets will be randomly assigned into 2 groups: 15 will receive α-CSH as a bone graft, while the other 15 will not receive any graft material. The main end point will be evaluated 6 months into the procedure. During follow-up visits, any adverse events or serious adverse events will be carefully documented, and clinical assessments will be conducted as specified in the “intervention section.” All patients will undergo regular monitoring through clinical examinations, radiographs, lab tests, and any additional necessary procedures. Ultimately, the study will publish a comprehensive report on the feasibility and potential efficacy of the α-CSH approach in promoting bone formation, regardless of the outcome.

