### Inclusion and Exclusion Criteria

To be eligible for participation in this clinical trial, patients must meet specific inclusion criteria, which are as follows: being a healthy male or female; aged 18-35 years old; providing written informed consent to participate in the trial; having an average blood count within normal range; presenting with impacted mandibular third molars that require extraction. The diagnostic indications for tooth extractions include caries, orthodontic, and preventive measures. In particular, based on the relation of the impacted mandibular third molar to the ramus, the impacted teeth will be restricted to Class I and Class II as per the Pell and Gregory classification [20,21]. Patients had to demonstrate good oral hygiene, maintain healthy periodontium, and have a clinical attachment loss score of ≤2 mm and a probing pocket depth (PPD) of <4 mm. Clinical and radiographic images taken before the operation are depicted in Figure 2.

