### Interventions

Prior to the surgical procedures, a preoperative panoramic x-ray and cone-beam computed tomography (CBCT) scan will be conducted to evaluate the tooth position and the surrounding bone structure. A complete blood count (CBC) will also be performed to ensure the safety of all patients undergoing surgical procedures and receiving bone grafts. Furthermore, the PPD score will be measured using a periodontal probe (BPWHO: Single, Osung, South Korea) to evaluate the periodontal condition. Patients exhibiting a significant amount of calculus will be referred for scaling and root planning procedures. Skilled oral and maxillofacial surgeons will carry out the interventions following standardized operating procedures. Video demonstrating the clinical and surgical procedures will be presented during the initial calibration meeting to ensure consistency across all operators.

The extraction of mandibular third molars will be carried out in a sterile environment under local anesthesia, minimizing damage to both the soft tissue (gingiva) and the hard tissue up to the crest of the bone. The surgery will adhere to the principle of minimally invasive techniques, using a split technique. To preserve the integrity of the marginal alveolar bone, an elevator will be used carefully to avoid any harm to the bone margins. Initially, a triangular access flap was created, with a releasing incision made on the tuberosity and another distal to the second molar. Then, the third molars will be split, and extraction will be performed using forceps or a dental elevator. After removing the tooth, a thorough sharp curettage will be performed to eliminate any remnants of the periodontal ligament and other soft tissues. Special attention will be given during the procedures to protect the socket walls and interproximal papillae from damage.

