### Adverse Event and Severe Adverse Event Assessment

Adverse events encountered during the study will be classified as serious or nonserious based on severity using the classification system established by the World Health Organization [22]. Participants who experience any adverse events will receive comprehensive medical care to address their needs. Any changes in the participant’s health status that occur between

the screening examination and the initial administration of α-CSH or associated procedures will be documented in their medical records. In the event of a severe adverse event, the principal investigator will be promptly notified within 24 hours of its occurrence. If the severe adverse event is determined to be associated with severe toxicity or infection at the transplant site, the experiment will be immediately halted to ensure participant safety.

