### Outcomes

#### Feasibility Assessment

The assessment of α-CSH safety in the present context will focus on the occurrence of serious adverse events. To deem α-CSH as safe, it should not result in a higher frequency of adverse events compared to standard treatment (without socket preservation). Additionally, any adverse events that do arise should be manageable through established noninvasive procedures such as analgesics and antibiotics. The evaluation of safety will play a crucial role in determining the suitability and viability of α-CSH in the study.

Feasibility evaluation was conducted using intraoral clinical examination and photographs to assess potential complications such as inflammation, infection, dehiscence, and graft loss. Graft loss will be evaluated in the early postoperative period, within the first week, and late postoperative period. The progress of wound healing at the surgical sites will be assessed with the Landry wound healing index [23]. This index considers factors such as the color of the soft tissue (pink or red), presence of suppuration, amount of bleeding, presence of granulation tissue, and exposure of connective tissue. Based on these criteria, the healing process was categorized into 5 distinct categories, namely very poor, poor, good, very good, and excellent [23]. Patients were also asked about any pain in the surgical site or adjacent areas during the follow-up period.

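### Half of the risks named for disclosure before enrolment match nothing in the described operation, and graft loss and graft-site toxicity are not named

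*Protocol article*

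**What the plan says.** In the protocol article, Recruitment promises each patient, before enrolment, "detailed information regarding the risks and potential complications associated with the procedure" and gives as examples "such as bleeding, infection, cheek asymmetry, parotid duct injury, potential injury to facial nerve branches, and the unlikely event of nonclosure". No other part of the article lists risks to be disclosed.

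Study Design defines the setting as "30 targeted extraction sockets after the removal of impacted mandibular third molars". Interventions describes a triangular flap, splitting and removal of the tooth, and curettage. The socket is then filled with α-CSH in the experimental group only, covered with a membrane and closed primarily with absorbable sutures.

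Two sections name complications. Under Feasibility Assessment, examinations and photographs are used to "assess potential complications such as inflammation, infection, dehiscence, and graft loss", and graft loss has its own early and late assessment. Under Adverse Event and Severe Adverse Event Assessment, the trial is halted if a severe event is judged to be "associated with severe toxicity or infection at the transplant site".

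Ethical Considerations says that the consent document "will comprehensively outline" the purpose, procedures, risks and benefits. The inclusion criteria require "providing written informed consent to participate in the trial".

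**The concern.** An article may shorten a list of risks. Shortening does not explain items that have no counterpart in the operation described. The examples also include nothing specific to the graft, which is the investigational element.

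What is at stake is the quality of disclosure. Written consent is a condition of entry, the article presents the study as the first in humans, and the Monitoring section dispenses with a separate data safety monitoring board on the ground of minimal risk. If the consent form follows the Recruitment list, participants would be told of risks unrelated to the surgery described. They would not be told of graft-specific events that the trial itself looks for or stops for.

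**Working it through.** No formula applies. The check sets the risk list against the procedure and against the complications named elsewhere in the article.

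**Step 1. Each disclosed risk against the described procedure and the named complications.**

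| Risk named in Recruitment | Counterpart in the article |
|---|---|
| Bleeding | Fits any extraction; bleeding is also a component of the wound healing index under Feasibility Assessment |
| Infection | Named under Feasibility Assessment and in the halting rule |
| Cheek asymmetry | None found |
| Parotid duct injury | None found |
| Facial nerve branch injury | None found |
| Nonclosure | Fits the primary closure in Interventions; close to dehiscence |

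Result: 3 of 6 fit, and 6 − 3 = 3 have no counterpart.

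**Step 2. Each named complication against the disclosed risks.**

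| Complication | Source | In the Recruitment list? |
|---|---|---|
| Inflammation | Feasibility Assessment | No |
| Infection | Feasibility Assessment; halting rule | Yes, in general terms |
| Dehiscence | Feasibility Assessment | Arguably, as nonclosure |
| Graft loss | Feasibility Assessment | No |
| Severe toxicity at the transplant site | Halting rule | No |

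Result: of the 4 complications under Feasibility Assessment, 1 is named, 1 is arguably covered and 2 are absent. Adding toxicity from the halting rule gives 5 in all: 1 named, 1 arguable, 3 absent.

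**Step 3. Who is affected.** Consent is given per participant, not per socket. The article fixes 30 sockets and says under Sample Size that the number per patient varies. The number of participants is therefore not stated; it is at most 30.

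**Step 4. Prior human use.** Sample Size says there are no earlier human data on this graft material, and the Abstract and Discussion call the study the first in humans. The Introduction says that α-CSH has already repaired bone defects, including in preserved extraction sockets, without saying in which species or with which preparation. These statements may be compatible, for instance if the earlier work was in animals or used another preparation, but the article does not say so. What a participant should be told on this point cannot be read from it.

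**Step 5. The incision.** Interventions says that "a triangular access flap was created, with a releasing incision made on the tuberosity and another distal to the second molar". In ordinary anatomical usage, tuberosity without further qualification points to the upper jaw, whereas Study Design places every socket in the lower jaw. This is a separate inconsistency in the surgical description.

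**The case against.** The strongest objection is that the consent form is not shown. Ethical Considerations says that it will set out risks in full, that participants may ask questions and review all procedures before signing, and that an ethics committee approved the trial. The Recruitment list is introduced by such as, so an item missing from it is not thereby withheld from patients. All of this stands. A reader might infer that consent is being given on the wrong risks, but the documents do not show what the form says.

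A reader might also infer that the whole list belongs to cheek or parotid surgery, or was carried over from another protocol. The first is too broad, because bleeding, infection and nonclosure fit this operation. The second cannot be settled from the documents; the incision wording is a reason to check and no more. Nor does the article say that patients here run no risk of the three unmatched injuries. It only describes nothing that would lead to them.

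The objection does not remove the mismatch itself. Examples given for a procedure should belong to that procedure, and a promise of full disclosure elsewhere does not make these three examples apt.

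**Conclusion.** The point holds as a mismatch in a stated disclosure rule. Three of the six risk examples match no described step and no named complication. Three of the five complications that the trial monitors or halts for (inflammation, graft loss, severe graft-site toxicity) are not among the examples. Counting nonclosure as covering dehiscence is a judgement in the protocol's favour; without it the absent count is four of five.

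The consequence for participants is conditional: it arises only if the consent form follows this list, which cannot be verified here. Prior human use is a point to reconcile, not a proven omission. The finding concerns participant protection and internal consistency. Randomisation, the endpoint, the 30-socket sample size and the analysis are untouched.

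**What to change.** 1. Reconcile the Recruitment list with the procedure in Interventions and with the complications under Feasibility Assessment and Adverse Event and Severe Adverse Event Assessment. Graft loss, dehiscence, inflammation and graft-site toxicity should be among the disclosed risks. Remove the three unmatched items, or state which part of the procedure gives rise to them.
2. Reconcile the Introduction with Sample Size on prior human use, and disclose the result to participants.
3. Check the consent form against the corrected list. Enrolment was under way when the article was written, so re-inform participants already enrolled, but only if the form carries the uncorrected list.
4. Separately, reconcile the incision description in Interventions with the lower-jaw site. Which wording is right is for the surgical investigators to say.

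The cost is a short text amendment, notification of the ethics committee and, at most, brief re-consent conversations. No statistical element has to change.

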**Figure 1 figure1:**
[figure not shown]
CONSORT (Consolidated Standards of Reporting Trials) flowchart diagram. α-CSH: α–calcium sulfate hemihydrate; PPD: probing pocket depth.

### Study Design

This prospective control clinical trial will be conducted at a single center and will involve 30 targeted extraction sockets after the removal of impacted mandibular third molars. This case is chosen as it represents a common scenario requiring extraction and often involving the removal of a significant amount of bone, making it an ideal model for studying human alveolar bone loss for socket preservation. The study aims to evaluate the efficacy of a high-purity α-CSH bioceramic (CaSO_4_·0.5H_2_O), synthesized from calcium sulfate dihydrate (CSD) without the use of chemical reagents, as a bone graft material in the alveolar bone loss case.

The 30 extraction sockets will be randomly assigned into 2 groups: 15 will receive α-CSH as a bone graft, while the other 15 will not receive any graft material. The main end point will be evaluated 6 months into the procedure. During follow-up visits, any adverse events or serious adverse events will be carefully documented, and clinical assessments will be conducted as specified in the “intervention section.” All patients will undergo regular monitoring through clinical examinations, radiographs, lab tests, and any additional necessary procedures. Ultimately, the study will publish a comprehensive report on the feasibility and potential efficacy of the α-CSH approach in promoting bone formation, regardless of the outcome.

